**Fig. 1. F1:**
[figure not shown]
Flowchart of the present study based on the CONSORT criteria. *Notes*. CONSORT = Consolidated Standards of Reporting Trials.

### Sample size calculation

Two groups (treatment vs. control group) will be compared over time (t_0_, t_1_, t_2_, and t_3_). Based on the results of previous PPU reduction interventions (Crosby, 2011; Crosby & Twohig, 2016; Minarcik, 2016), small effect sizes (Cohen *d* = 0.2) may be anticipated when comparing the treatment and control conditions. After calculations conducted with the G*Power software, a sample size of 121 in each study group would have 80% power to detect the difference with an alpha error of 5% and two-tailed testing. Therefore, the recruitment of a minimum of 242 participants would be sufficient to detect differences between the treatment and control groups over time.

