### Recruitment of study participants

The recruitment takes place since February 2019 and is currently ongoing until the target number of minimum participants is reached (*N* = 242). Participants will be recruited on pornography sites, psychology news websites, newsletters, and social media sites. The study will mainly recruit people from Switzerland and Hungary; however, participants from other countries will not be excluded. Participants will not be compensated for participation.

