However, some limitations of the present study should be mentioned. First, dropout rates are expected to be high in line with reports from previous online intervention studies (Rooke, Copeland, Norberg, Hine, & McCambridge, 2013; Schaub et al., 2015). Second, online interventions are often characterized by a low adherence rate because of the distant nature of the interventions (e.g., lack of personal relationships or non-personalized exercises) (Amann et al., 2018). Third, individuals with PPU who are currently receiving psychosocial or pharmacological treatments to reduce their PPU will be excluded from the study. Fourth, individuals who are more familiar with the use of the Internet may be more likely to participate in the study that may result in self-selection bias (Wantland, Portillo, Holzemer, Slaughter, & McGhee, 2004). Fifth, all measures will be self-reported, which may result in report bias. However, anonymous, online, self-reported data collection may be beneficial in sexuality-related studies when participants are asked to report about sensitive topics and problematic behaviors by alleviating stress resulting in more honest responses (Griffiths, 2012).

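### The 80% power claim assumes essentially complete follow-up: 242 is both the calculated sample size and the recruitment stop, with no allowance for the high dropout the protocol expects

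*Protocol article*

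**What the plan says.** The section Sample size calculation anticipates a Cohen d of 0.2 and reports from G*Power that "a sample size of 121 in each study group would have 80% power to detect the difference", at a two-tailed alpha of 5%. It then moves from the number the calculation returns to the number to enrol: "Therefore, the recruitment of a minimum of 242 participants would be sufficient to detect differences between the treatment and control groups over time".

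The section Recruitment of study participants fixes the stop at the same figure. Recruitment "is currently ongoing until the target number of minimum participants is reached", with N = 242 given in brackets.

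The limitations in the Discussion begin: "First, dropout rates are expected to be high in line with reports from previous online intervention studies". The Introduction also lists higher dropout among the disadvantages of online interventions. Neither place gives a rate.

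The section Data analyses plans an intention-to-treat analysis with multiple imputation, using demographic and other baseline measures as predictors, and linear mixed models over the repeated assessments. The primary outcome, the PPCS, is scheduled at baseline and at all three follow-ups (Table 3).

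**The concern.** One figure does two jobs. As the output of a power calculation, 121 per group is the number whose outcome data are needed. As a recruitment target, 242 is the number who enter. The two coincide only if nobody is lost, and the protocol expects the opposite.

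What is at stake is how a null result will be read. If the primary comparison is not significant, readers will weigh it against a stated 80% power. If the trial's real power is well below that because of dropout alone, the result says less against the program than the protocol implies.

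**Working it through.** **Inputs.** From Sample size calculation: d = 0.2, two-sided alpha 0.05, power 80%, 121 per group. From Recruitment of study participants: stop at 242. From Randomization and trial flow: 1:1 allocation. Assumed: the dropout rate and equal dropout in both arms.

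**1. The plan's own figure.** For two groups, n per arm = 2(1.960 + 0.842)²/d². With d = 0.2 this is 2 × 7.849/0.04 = 392.4, so 393, or 394 with the exact t distribution. At 121 per arm, power for d = 0.2 is 34%. So 121 does not reproduce as a two-group comparison. Some repeated-measures F tests of the group-by-time interaction with f = 0.1 come close to 242 in total, but only with correlations the protocol does not state: 248 with four measurements and correlation 0.1, 244 with three and 0.25, 238 with two and 0.4.

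**2. Is there an allowance?** 2 × 121 = 242, so recruitment equals the calculated number with nothing added. The text does not say that 121 already contains a margin.

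**3. Worst case: all loss occurs before the first follow-up (t1).** To isolate dropout, grant that 121 per arm with full data gives exactly 80%. In a two-sample t-test that corresponds to a standardised effect of 0.362. Power is recomputed at n = 121 × (1 − loss):

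| Loss | Left per arm | Power | Effect detectable with 80% power |
|---|---|---|---|
| 0% | 121 | 80% | 0.36 |
| 20% | 97 | 71% | 0.40 |
| 30% | 85 | 65% | 0.43 |
| 40% | 73 | 58% | 0.47 |
| 50% | about 60 | 51% | 0.51 |
| 60% | 48 | 42% | 0.58 |

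The 0.362 is a device to hold the plan's 80% fixed. It is not the protocol's target effect.

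**4. Staggered loss under a mixed model.** Assume a treatment effect that is constant over the follow-ups, compound symmetry with within-person correlation ρ, and retention of 80/65/50% at t1/t2/t3 with no returns. Then 20% give no follow-up score, 15% one, 15% two and 50% three. A person with k scores carries information k/[1 + (k − 1)ρ].

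- ρ = 0.5: the values are 1, 1.333 and 1.5. The mean is 0.15 × 1 + 0.15 × 1.333 + 0.50 × 1.5 = 1.10, and 1.10/1.5 = 0.733 of full information. Power = Φ(2.802 × √0.733 − 1.960) = Φ(0.44) = 67%.
- ρ = 0.3: 1.318/1.875 = 0.703, power 65%.
- ρ = 0.7: 0.951/1.25 = 0.761, power 69%.

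If the model also conditions on baseline PPCS, 69–72% of the information remains and power is about 64–66%. Either way, 50% loss by t3 costs less than the 51% in the table suggests, but power still falls 11 to 16 points short of 80%.

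**The case against.** Several points on the other side are fair.

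- **All 242 are analysed.** A reader might infer that the trial cannot deliver the analysed number behind the power claim. The documents do not support that wording, because intention-to-treat with multiple imputation and mixed models keeps every randomised participant in the analysis. What is lost is information. For someone with no post-baseline PPCS, baseline predictors say essentially nothing about the difference between arms, and valid imputation standard errors reflect this.
- **Partial follow-up counts.** The primary outcome spans three follow-ups, so a participant who leaves after t1 still contributes. This stands, and it is why step 3 is a worst case.
- **The 121 may contain slack.** One interaction calculation (f = 0.1, four measurements, correlation 0.5) needs only 138 in total, so hidden slack cannot be strictly excluded. But the protocol presents 121 as the number that gives 80%, and the plain two-group reading of its inputs points to a shortfall.
- **The target is a minimum.** That would leave room to recruit more, but the recruitment section ends enrolment when the minimum is reached, and the sample size section calls that minimum sufficient.
- **The dropout is disclosed, and 2 × 121 is correct.** Both are true. The fault is an omitted allowance, not a multiplication error. Listing dropout as a limitation does not adjust the power claim.
- **No rate is given.** This also stands. The size can only be shown as a range.

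**Conclusion.** The point holds in this form: the stated 80% power requires essentially complete follow-up PPCS data, and the protocol's own dropout expectation contradicts that. Granting 80% at 121 per arm with full data and equal dropout, power is about 71%, 65% and 51% at 20%, 30% and 50% loss if all loss precedes t1. It is about 65–69% with 80/65/50% retention, a constant effect and correlation 0.3–0.7 (64–66% if baseline is also conditioned on). The direction is clear; the size depends on assumed rates and on when people leave.

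Two stronger inferences are not supported. The table does not give this trial's actual power, because the dropout rate is unknown and the starting 80% is granted, not confirmed. Nor does the point show that 121 per arm with follow-up data would be enough: for d = 0.2 in a two-group comparison it would give 34%. That base figure is a separate problem to settle first.

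**What to change.** In Sample size calculation, say that 242 is the number randomised and that the 80% figure assumes complete follow-up. Replace the sufficiency claim with the power, or the detectable effect, at the expected retention, shown over a range of dropout rates and stating whether loss is taken to occur before t1 or to be spread over the follow-ups. The online trials already cited in the Discussion are a natural source for the expected rate.

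Do this from a corrected base calculation that names the test, the effect measure and any within-person correlation. Do not restate 121 per group as the number required.

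The cost is one rewritten paragraph and one recalculation. Correcting the claim needs no added enrolment, visits or staff. The only downside is a less favourable stated power.

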### Recruitment of study participants

The recruitment takes place since February 2019 and is currently ongoing until the target number of minimum participants is reached (*N* = 242). Participants will be recruited on pornography sites, psychology news websites, newsletters, and social media sites. The study will mainly recruit people from Switzerland and Hungary; however, participants from other countries will not be excluded. Participants will not be compensated for participation.

### Registration and consent procedure

Participants will register online by providing minimal personal data, including their e-mail address and necessary sociodemographic information (e.g., age, gender). Informed consent will be obtained before enrollment in the study. Participants will be assigned to be randomized if they are eligible according to the inclusion and exclusion criteria (see Table 1).

**Table 1. T1:** Inclusion and exclusion criteria in the present study

Inclusion criteria	Rationale
1. Minimum age of 18	To ensure the minimum age of participation
2. Proficiency in English (at least intermediate level)	To ensure that participants will be able to understand the information provided
3. Internet access at least once every week and a valid email address	To ensure access to the intervention
4. Completion of the informed consent	To ensure knowledge of procedures and the declaration of consent

Exclusion criteria	Rationale
1. Self-reported engagement in other treatment for problematic pornography use	To avoid confounding treatment effects

### Randomization and trial flow

After the baseline assessment, randomization will take place at an individual level by an automated, computer-based algorithm on the intervention website. A randomization list will be created in a 1:1 ratio. After the randomization, participants in the intervention condition will receive immediate access to the online intervention, while participants in the control condition will receive access to the intervention three months after the completion of the baseline questionnaire. Participants will know to which group they have been assigned. The intervention condition will last six weeks. Follow-up assessments will be completed online and will take place right after the end of the six-week-long intervention (t_1_), at a one-month follow-up (t_2_), and three-month follow-up (t_3_) (Fig. 1). If the final assessment is not completed, up to two reminders will be sent out 2 and 5 days later.

### Hypotheses

Concerning the primary outcome, we hypothesize that participating in the intervention condition (study arm 1)—compared to the control condition (study arm 2)—will result in lower levels of PPU comparing the baseline and the follow-up assessments. Regarding the secondary outcomes, we hypothesize that participating in the intervention condition—compared to the control condition—will result in lower levels of pornography use frequency, lower levels of pornography craving, lower levels of negative emotions in general, higher levels of sexual satisfaction, higher levels of pornography avoidance self-efficacy, higher levels of beliefs about the malleability of sexual life, higher levels of life satisfaction, and higher levels of positive emotions in general over time.

### Intervention

Hands-off (www.hands-off.net) is an automated online self-help program developed by the authors of this paper to reduce PPU. The program includes a dashboard, a pornography use diary, six treatment modules, and a booster module that were developed to reduce PPU. The program was developed based on the principles of motivational interviewing (Rollnick & Miller, 1995), cognitive-behavioral therapy (Meichenbaum, 1977), mindfulness techniques (Altman, 2014), and “wise” social-psychological interventions (Walton, 2014; Walton & Wilson, 2018; Yeager & Walton, 2011). The modules were created based on previous online interventions developed by the Swiss Research Institute for Public Health and Addiction that effectively reduced substance use, alcohol use, and problematic gambling (Baumgartner et al., 2019; Schaub et al., 2016, 2013). The core modules (1–6) must be completed in their intended sequence (i.e., finishing each module unlocks access to the next one). The booster module can be completed one-month after finishing the intervention condition. It was designed to reflect on the difficulties after finishing the program and to motivate the participants further to implement the acquired knowledge in their everyday life. Participants are encouraged to repeat any modules if they feel they need to.

### Intervention condition - Study arm 1

#### Dashboard

The main page is the dashboard. It was created to provide useful information quickly and to display the dates of the follow-up assessments. The participants can also enter their pornography use information directly from the past week, and they can plan their target frequency of pornography use for the next week as well. An activity planner is also included on the dashboard that reminds the participants to plan activities for the current week and rate their level of anticipated and actual enjoyment of the given activity (Fig. 2).

**Fig. 2. F2:**
[figure not shown]
Dashboard in the intervention condition. *Notes*. The information included in the figure is based on fictional data.

#### Self-help intervention modules

Six self-help intervention modules and one booster module are included in the intervention condition presented in the Modules section of the website (Fig. 3). A summary of each module's content is presented in Table 2. Participants are encouraged to complete one module each week. As mentioned above, modules 1–6 can only be completed in their intended sequence, and the booster module can only be completed one-month after finishing the intervention condition. Participants are encouraged to repeat any modules if they would find it helpful. Red bars indicate any progress the participants have already made within each module; green bars indicate if modules are completed.

**Fig. 3. F3:**
[figure not shown]
Overview of the treatment modules in the intervention condition.

**Table 2. T2:** Modules in the intervention condition

Modules	Content
*Module 1*: Introduction and the possibility of change	• General overview • Introduction to fictional companions • Reflections on personal pornography use (e.g., advantages and disadvantages, reasons for change, reviewing useful resources for a change)
*Module 2*: Why do I watch porn, and how can I change it? Identifying internal and external risk situations	• Identification of the internal and external risk situations that can lead to pornography use • Learning how to deal with these risk situations
*Module 3*: How to feel better without porn?	• Learning how to change personal pornography using habits • Learning how to integrate joyful activities into everyday life
*Module 4*: What can I do about my cravings?	• Identification of personal triggers for cravings • Learning strategies to reduce craving
*Module 5*: Behaviors, Emotions, and Thoughts (BET): I BET you can do it	• Getting to know automatic negative thoughts and the most frequent common thinking errors • Learning about the relations between one's thoughts, emotions, and pornography use • Learning strategies to challenge automatic negative thoughts and develop balanced thoughts
*Module 6*: How to preserve your success?	• Reviewing the main contents of the previous modules • Identification of one's toughest moments in the program and how he/she overcame them • Planning strategies to prevent relapses to previous pornography use habits
*Booster module*: Success in the long run	• Reviewing one's past month and the strategies he/she used to reduce his/her pornography use and to improve his/her mood • Making plans for the future to preserve success in the long run

#### Pornography use diary

After the completion of the first module, there will be daily assessments of pornography use (frequency of use per day) and mood (Positive and Negative Affect Scale – PANAS (Gyollai, Simor, Köteles, & Demetrovics, 2011)) (Fig. 4). Participants will be asked to record their targeted (i.e., how much pornography they want to use over the upcoming week) and their actual pornography use (i.e., how much pornography they used during the past week). Additionally, they can register their mood each day. A personal graph will be generated with their inputs for visual feedback. Setting daily pornography use goals may strengthen the participants' self-efficacy, while mood tracking may contribute to the identification and understanding of the relationships between their mood and pornography use.

**Fig. 4. F4:**
[figure not shown]
A week sample of the pornography use and mood tracker diary in the intervention condition.

#### Fictional companions

Four fictional companions were created representing typical problematic pornography users to encourage reflection on specific questions in each module (Fig. 5). These companions share their thoughts, fears, and achievements in written form. Participants can choose one character that they best identify with based on their situation but may also view the input provided by the other companions by clicking on their icons.

**Fig. 5. F5:**
[figure not shown]
Fictional companions in the intervention group.

#### Safety

During the participation in the program, participants are provided with an emergency button (“Help Me” tab) for immediate responses to frequently asked questions and access to emergency contacts (Fig. 6). Participants will be informed about how to use this information.

**Fig. 6. F6:**
[figure not shown]
Emergency information in the intervention group.

#### Other elements

In some exercises (e.g., pros and cons of pornography use), participants will be asked to enter their answers by clicking on checkboxes or entering text freely. This information will be accessible for them anytime in their Profile (“My inputs” section). Entering information during the program would not only result in higher levels of engagement but may also be considered as an effective self-persuasion technique (Aronson, 1999; Sniewski & Farvid, 2019). Moreover, adherence to the treatment will be monitored, and reminders will be sent via e-mails after seven (14, 21, 28) days of non-compliance (i.e., not logging in to the intervention website or not completing the daily diary of pornography use and mood).

### Control condition – Study arm 2

Participants randomized to the wait-list control group will be provided the opportunity to participate in the intervention condition (study arm 1) three months after registration. Participants will also complete the baseline (t_0_) and the follow-up (t_1_, t_2_, and t_3_) assessments.

### Measures

Sociodemographic data will include gender, age, level of education, socio-economic status, religious views, place of residence, relationship status, and sexual orientation. Sexuality-related questions will include the number of lifetime sexual partners and the number of lifetime casual sexual partners (Bőthe, Bartók et al., 2018a). Table 3 provides an overview of and a schedule for the measures that will be administered.

**Table 3. T3:** Schedule for the assessment of study variables

Assessment instruments	Baseline (t_0_)	After finishing the program (t_1_)	One-month follow-up (t_2_)	Three-month follow-up (t_3_)
**Sociodemographic questions**	X			
**Pornography use-related measures**	X	X	X	X
Pornography use-related questions (frequency of use, duration of use per occasion)	X	X	X	X
Previous treatment for problematic pornography use	X			
Problematic pornography use (PPCS)	X	X	X	X
Self-reported perceived addiction to pornography use	X	X	X	X
Moral incongruence regarding pornography use	X	X	X	X
Pornography craving (PCQ)	X	X	X	X
Pornography avoidance self-efficacy (PASS)	X	X	X	X
**Sexuality-related measures**	X	X	X	X
Sexuality-related questions	X	X	X	X
Sexual satisfaction	X	X	X	X
Beliefs about the malleability of sexual life (SMS)	X	X	X	X
**Life quality measures**	X	X	X	X
Life satisfaction (SWLS)	X	X	X	X
General positive and negative emotions (PANAS)	X			X
**Psychopathological symptoms measures**	X	X	X	X
Depression, anxiety, and somatization (BSI-18)	X	X	X	X
ADHD (ASRS-5)	X	X	X	X
Substance use (NIDA)	X	X	X	X
Alcohol use (SIP)	X	X	X	X
Suicide risk (P4)	X	X	X	X
**Side effects (wanted and unwanted effects)**		X		

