## Methods

### Study design

The web-based (online) self-help program, Hands-off, will be evaluated with a two-armed RCT comparing the efficacy of the (1) intervention condition with the (2) wait-list control condition. Participants assigned to the control condition will access the intervention materials three months after completing the baseline questionnaire set. Participants will be unaware of the hypotheses of the study but will be aware of the assigned condition. Any blinding of study personnel is unwarranted, as they will not be directly involved in the intervention or the assessment. After completing the baseline self-report questionnaire (t_0_), participants will be randomly assigned to one of the two study arms. Further assessments will take place right after the end of the six-week-long intervention (t_1_), at a one-month follow-up (t_2_), and three-month follow-up (t_3_) after the end of the intervention (Fig. 1). The study was preregistered on the Open Science Framework (OSF) Website (https://osf.io/5tqkb/).

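### Positive and negative affect (PANAS) is scheduled only at baseline and t3, so neither affect hypothesis has a post-baseline comparison with controls not yet offered the program

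*Protocol article*

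**What the plan says.** **Schedule.** In Table 3 (Measures section), the row "General positive and negative emotions (PANAS" has a mark at t0, blanks at t1 and t2, and a mark at t3. Frequency of use, craving, avoidance self-efficacy, sexual satisfaction, sex mindset and life satisfaction are all marked at t0, t1, t2 and t3.

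**Hypotheses.** Both affect scores are hypothesised secondary outcomes. The Hypotheses section predicts, for the intervention arm relative to control, "lower levels of negative emotions in general" and "higher levels of positive emotions in general over time". The last paragraph of the Introduction also lists both among the secondary outcomes to be compared with the control group.

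**Control access.** The Study design section states: "Participants assigned to the control condition will access the intervention materials three months after completing the baseline questionnaire set". Randomization and trial flow repeats that "participants in the control condition will receive access to the intervention three months after the completion of the baseline questionnaire". The section on the control condition (Study arm 2) counts from a different origin: controls "will be provided the opportunity to participate in the intervention condition (study arm 1) three months after registration".

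**Visit timing.** Randomization and trial flow gives the length of the program: "The intervention condition will last six weeks". Study design places the last visit at the "three-month follow-up (t_3_) after the end of the intervention".

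**The concern.** A hypothesis about the program against a wait-list needs at least one post-baseline measurement taken while the wait-list is still waiting. For the two affect scores the schedule provides none. Their only post-baseline value is taken after controls have been offered the same program, with enough time elapsed for a control participant to have worked through all of it.

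The late control offer affects every outcome at t3, including the primary one. The other hypothesised outcomes can fall back on t1 and t2; the affect scores cannot. What is at stake is the interpretation of two secondary results. A small or null t3 difference in affect could mean that the program does not change affect, or that controls had partly caught up, and the data could not tell these apart. No analysis method repairs this: multiple imputation and mixed models cannot recover t1 and t2 affect values that were collected in neither arm.

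**Working it through.** The article states no figure to reproduce here. The check is arithmetic on the timeline, followed by a count of visits and the size of the possible dilution.

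**1. Inputs**
- Program length: 6 weeks = 42 days (Randomization and trial flow).
- t1: at the end of the program. t2 and t3: one and three months after its end (Study design).
- Control access: three months after baseline (Study design; Randomization and trial flow).
- Month length M: not defined, so varied from 28 to 31 days.
- Assumption: both arms are assessed on the same calendar, counted from baseline.

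**2. Timeline, in weeks from baseline**

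| Event | Formula (days) | M = 28 | M = 30 | M = 31 |
|---|---|---|---|---|
| t1 | 42 | 6.0 | 6.0 | 6.0 |
| t2 | 42 + M | 10.0 | 10.3 | 10.4 |
| Control access | 3M | 12.0 | 12.9 | 13.3 |
| t3 | 42 + 3M | 18.0 | 18.9 | 19.3 |

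Gap from control access to t3: (42 + 3M) − 3M = 42 days = 6.0 weeks for any M, the full length of the program.

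Lead of t2 over control access: 3M − (42 + M) = 2M − 42 days, which is 14 days (2.0 weeks) at M = 28 and 20 days (2.9 weeks) at M = 31.

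If access is instead counted from registration, which precedes the baseline questionnaire, access comes earlier. The gap to t3 is then at least 6 weeks, and t2 still precedes access provided the lag from registration to baseline is shorter than that 2.0 to 2.9 week margin.

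**3. Visits after baseline and before control access**
- Other hypothesised secondary outcomes: t1 and t2, so 2 of 3 follow-ups.
- PANAS: 0 of 3 follow-ups.

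**4. Could another source fill the gap?** The Pornography use diary section describes daily mood ratings with the PANAS. The diary is part of the intervention condition and opens after module 1, so it yields no control data before controls gain access. The Secondary outcomes section describes the PANAS as measuring present feelings, so a t3 score does not look back to the period before access.

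**5. Size of the dilution at t3.** Let Δ be the true effect on affect against an untreated wait-list. Let p be the share of Δ that the control arm, averaged over users and non-users of the program, has gained by t3. If the intervention arm keeps its effect, the expected t3 difference is Δ − pΔ = (1 − p)Δ.

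| p (assumed) | Expected t3 difference |
|---|---|
| 0 | 1.00 Δ |
| 0.25 | 0.75 Δ |
| 0.50 | 0.50 Δ |
| 0.75 | 0.25 Δ |
| 1 | 0 |

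The article gives no control uptake or response figure, so p cannot be placed within this range.

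**The case against.** **The t3 comparison is still randomised.** This stands. A reader might infer that the two affect outcomes have no valid controlled measurement at all. The article does not support that: t3 is an intention-to-treat comparison of the randomised arms. It answers a different question, immediate versus delayed access, and as an estimate of program versus wait-list it is probably diluted.

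**Access is not exposure.** This also stands. The article offers controls an opportunity to take part, encourages one module a week in fixed order, and in the Discussion expects high dropout and low adherence. A reader might infer that a true benefit would be reported as absent. That requires full catch-up by the whole control arm within six weeks (p = 1), the extreme of the range. Low uptake would put p nearer 0. Since p is not given, neither end can be claimed.

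**The blanks may be a slip in the table.** Possible. The hypotheses speak of change over time, and the control-condition section says that controls complete t1, t2 and t3 without excepting the PANAS. The group heading for life quality measures is marked at all four visits, but the life satisfaction row alone would explain that. No text places the PANAS at t1 or t2, so the table has to be taken as it stands until the sponsor confirms it.

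**The cause is shared and the outcomes are secondary.** True. The missing t1 and t2 measurements are nevertheless specific to the PANAS, and giving t1 and t2 more weight in the analysis would not create them. The primary conclusion is not affected by this point.

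**Not every item listed under secondary outcomes is measured four times.** Previous treatment-seeking is recorded at baseline only, but it is history and no hypothesis concerns it.

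**Conclusion.** The concern holds in a limited form. As scheduled, the two affect hypotheses have no post-baseline comparison with a wait-list not yet offered the program: 0 of 3 follow-ups, against 2 of 3 for the other hypothesised secondary outcomes. The one available contrast comes six weeks after the control offer and estimates (1 − p) of the true effect, anywhere from all of it to none.

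This rests on three assumptions: that Table 3 is the intended schedule, that both arms are assessed on the same calendar from baseline, and, for the dilution formula, that the intervention arm keeps its effect to t3. The six-week gap does not depend on the month length. The point should be settled while recruitment is still open. It is a weakness in two secondary outcomes, not a flaw in the trial's main result.

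**What to change.** 1. Confirm whether the blank t1 and t2 cells in the PANAS row are intended, and reconcile Table 3 with the Hypotheses section and the last paragraph of the Introduction. If the blanks are a slip and the PANAS is already collected at those visits, correcting the table is enough for the schedule.
2. If the blanks are intended, add the ten-item PANAS at t1 and t2 in both arms, in Table 3 and on the study website.
3. State that t1 and t2 are the main arm comparison for positive and negative affect, and that the t3 PANAS result is reported as immediate versus delayed access.
4. State the origin from which control access is counted, since baseline and registration are both given.

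This leaves the timing of control access unchanged.

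**Cost.** Ten more items at each of two online visits that both arms already complete. Recruitment has run since February 2019, so participants already past t1 or t2 will lack these values. The t1/t2 comparison should be limited to participants of both arms whose visit falls due after the change, using the same cut-off rule in each arm, with the reduced number stated.
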